#### Laboratory investigations

Laboratory investigations are not mandated for the trial. However it is recommended that all enrolled patients have screening for respiratory viruses using nasopharyngeal aspirate completed to provide data on the various viruses amongst the recruited patients. The screening will occur at the discretion of the managing physician.

### Time frame

It is predicted that patient enrolment will occur over a period of three years. Individual participant study involvement will cease at death or discharge home.

### Healthcare cost analysis

A within-trial economic evaluation will be undertaken from the health care provider perspective using a cost-minimisation approach, to compare the cost of providing HFNC therapy to that of standard subnasal oxygen therapy. This approach assumes a reasonable and equivalent clinical outcome at the point of discharge to home. Resources to be measured and costed will include the number of transfers between hospitals, length of stay (in PICU and/or non-intensive stay), and resources related to use of the intervention (HFNC therapy or standard subnasal oxygen therapy). Costs will be assigned using standard costing sources [24]. The Australian refined diagnostic-related groups (AR-DRG) will be used to indicate the costs associated with each hospital admission, adjusted for length of stay in hospital and in PICU. The New Zealand centres health care costs will be analysed separately and sensitivity analysis for the different health care system will be performed. Parametric (e.g. ANCOVA) and non-parametric bootstrapping techniques will be employed to compare the costs between groups, and to estimate a confidence interval around the mean difference [25]. It is anticipated that HFNC therapy will be cost saving to the health system. The cost comparison will inform recommendations on adopting HFNC therapy for the management of bronchiolitis in clinical practice.

### Sample size, power and statistical methods

#### Sample size

In 2011 there were 478 eligible patients admitted to 4 of 8 pilot hospitals (Queensland), of which 80 required transfer to a tertiary paediatric centre (16.7 %). Assuming a conservative baseline rate of failure of standard therapy (need for transfer to a specialist paediatric centre or PICU admission) of 10 %, a 50 % relative reduction to 5 % with a power of 90 % and type I error of 0.05, 582 participants per group are required, resulting in a total sample size of 1164 patients. An attrition rate of approximately 10-20 % is estimated, which gives an overall sample size of 1400.

#### Data analysis

Descriptive statistics will be utilised to report on the baseline characteristics of the total study cohort, as well as by site. The primary outcome measure investigating clinical treatment failure will be analysed using test of two proportions, and will be reported as the difference, 95 % confidence interval and *p*-value. The secondary outcome measure investigating length of stay will likely be non-normally distributed, and as such will be analysed using a Mann-Whitney U test; if it is normally distributed independent samples t-test will be used. Analysis of secondary outcomes includes both comparisons of measurements and proportions, using confidence intervals of differences as the major method of presentation where possible. A logistic regression analysis will be used to identify risk factors. All analyses will be by intention-to-treat. A per protocol analysis will be undertaken as a secondary analysis. Pre-specified sub-groups include; ex-preterm infants, infants with congenital heart defect, infants less than 3 months of age (corrected), infants less than 6 months of age (corrected), infants presenting to tertiary sites, infants presenting to secondary sites. Statistical significance will be set at the 0.05 level. No interim analysis will occur and no stopping rules were defined.

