**Methods/Design:**

Prospective multi-centre randomised trial comparing standard treatment (standard subnasal oxygen) and High Flow Nasal Cannula therapy in infants with bronchiolitis admitted to 17 hospitals emergency departments and wards in Australia and New Zealand, including 12 non-tertiary regional/metropolitan and 5 tertiary centres. The primary outcome is treatment failure; defined as meeting three out of four pre-specified failure criteria requiring escalation of treatment or higher level of care; i) heart rate remains unchanged or increased compared to admission/enrolment observations, ii) respiratory rate remains unchanged or increased compared to admission/enrolment observations, iii) oxygen requirement in HFNC therapy arm exceeds FiO_2_ ≥ 40 % to maintain SpO_2_ ≥ 92 % (or ≥94 %) or oxygen requirement in standard subnasal oxygen therapy arm exceeds >2L/min to maintain SpO_2_ ≥ 92 % (or ≥94 %), and iv) hospital internal Early Warning Tool calls for medical review and escalation of care. Secondary outcomes include transfer to tertiary institution, admission to intensive care, length of stay, length of oxygen treatment, need for non-invasive/invasive ventilation, intubation, adverse events, and cost.

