#### Clinical observations

SpO2 will be measured at enrolment in room air. If the infant has had oxygen administered in the ambulance, then it will be ceased and SpO2 assessed a few minutes later to ascertain if the infant meets the inclusion criteria of SpO2 < 92 % (<94 %). Once this inclusion criteria has been established, respiratory rate, respiratory effort and heart rate will be measured at enrolment. Observations thereafter will be according to current hospital protocol within either the ED or general paediatric ward.

At each set of observations, the following parameters will be documented: SpO2, heart rate, respiratory rate, respiratory effort, oxygen/FiO2 administered, flow rate of high flow therapy and at frequent intervals the temperature and blood pressure will be monitored according to standard hospital guidelines.

Complications recorded will include episodes of apnoea and bradycardia (lasting more than 20 seconds); all episodes where the SpO2 was recorded <92 % (94 %) and adverse outcomes such as pneumothoraces or deaths.

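### The primary test is valid but unadjusted: enrolment severity is already recorded, and a pre-specified adjusted risk difference would add a little precision at small cost

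*Protocol article*

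**What the plan says.** The Data analysis section of the protocol article fixes the primary method: "The primary outcome measure investigating clinical treatment failure will be analysed using test of two proportions", with the result given as a difference, its 95% confidence interval and a p-value. It names no covariate and no stratification factor for this comparison. The only regression it names for clinical outcomes is a logistic model to look for risk factors, separate from the treatment comparison.

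The Clinical observations section shows what is available before treatment: "SpO2 will be measured at enrolment in room air", and then "respiratory rate, respiratory effort and heart rate will be measured at enrolment". Corrected age and prematurity must also be known, because the Data analysis section defines subgroups by them. The Randomisation process section allocates 1:1 per site and states no stratification by severity.

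Enrolment values also enter the outcome itself. One of the four failure criteria is that "heart rate remains unchanged or increased compared to admission/enrolment observations", and the respiratory-rate criterion has the same form.

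**The concern.** Balance between arms on severity rests on chance alone, and the primary estimate makes no use of severity values the trial will already hold. Two things follow. Variance in failure that those values could explain stays in the confidence interval. If the arms happen to differ in severity, the crude difference carries that shift and the analysis does not take it out.

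Using enrolment heart rate and respiratory rate as the reference for two criteria is not adjustment for them. Whether a rate has failed to fall since enrolment still depends on where it started. The article names the primary method outright, so a statistical analysis plan that made an adjusted analysis primary would depart from it.

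**Working it through.** **Inputs from the article (Sample size).** Failure 10% in control and 5% with HFNC, power 90%, type I error 0.05: "a 50 % relative reduction to 5 % with a power of 90 % and type I error of 0.05". The stated result is that "582 participants per group are required, resulting in a total sample size of 1164 patients". The section glosses the 10% as need for transfer or PICU admission, not as the three-of-four failure criteria. The rates are used here as the plan's own.

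**Input not in the article.** The prognostic strength of enrolment severity. Assumption: one normally distributed severity score with an odds ratio (OR) for failure of 1.0 to 3.0 per SD.

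**Step 1: reproduce 582.** Two-sided test, pooled variance, mean rate 0.075:

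n = [1.960 × √(2 × 0.075 × 0.925) + 1.282 × √(0.10 × 0.90 + 0.05 × 0.95)]² / 0.05²
= (0.730 + 0.475)² / 0.0025 = 581.1, rounded up to 582.

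The plan's figure therefore reproduces under exactly the crude test it names.

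**Step 2: crude precision.** SE = √(0.1375 / 582) = 0.0154, so the 95% CI half-width is 1.96 × 0.0154 = 0.030, or about 3.0 percentage points.

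**Step 3: gain from adjustment.** Let X be the severity score, with logit p_k(X) = a_k + ln(OR) × X in arm k and a_k set so that the average risks stay at 10% and 5%. The large-sample variances, per n per arm, are

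- crude: 0.10 × 0.90 + 0.05 × 0.95 = 0.1375
- adjusted and standardised: E[p0(1−p0)] + E[p1(1−p1)] + Var(p1−p0)/2

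With r the proportional reduction in variance, power is read at an effective size of 582/(1−r) per group, and likewise for 700 per group (all 1400 analysed).

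| OR per SD | r | Effective n per group | Power at 582 | Power at 700 |
|---|---|---|---|---|
| 1.0 | 0% | 582 | 90.0% | 94.5% |
| 1.5 | 1.2% | 589 | 90.4% | 94.7% |
| 2.0 | 3.5% | 603 | 91.0% | 95.2% |
| 2.5 | 6.3% | 621 | 91.8% | 95.7% |
| 3.0 | 9.0% | 640 | 92.5% | 96.2% |

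At OR 1.5 to 2.0 the gain is worth about 2 × 7 = 14 to 2 × 21 = 42 infants in total, and the confidence interval narrows by 0.6% to 1.8%.

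**Step 4: check by simulation.** In 4,000 trials per setting, comparing the crude z-test with the Wald test from an adjusted logistic model, power at 582 per group was 90.8% v 91.0% (OR 1.5), 90.0% v 91.0% (OR 2.0) and 90.5% v 92.6% (OR 3.0). Monte Carlo error is about √(0.9 × 0.1 / 4000) = 0.5 points, so the simulation agrees in scale but cannot resolve the smallest gain. With both rates at 10%, crude type I error was 4.6% to 5.6% over all settings.

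**Step 5: chance imbalance.** The standardised baseline difference between arms has standard error √(2/582) = 0.059, so two standard errors are 0.117 SD. The mean of p(1−p) over the two arms is 0.1375/2 = 0.06875. The shift in the crude difference is about 0.06875 × ln(OR) × 0.117:

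- OR 1.4: 0.06875 × 0.336 × 0.117 = 0.0027, about 0.3 points
- OR 1.8: 0.06875 × 0.588 × 0.117 = 0.0047, about 0.5 points

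The half-width is about 3 points and the planned effect is 5 points.

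**The case against.** The strongest reply is that nothing here is wrong. Under 1:1 randomisation the two-proportion test is valid, yields the promised risk difference without a model, and is the test the sample size was built on. That stands. A reader might infer from the lack of adjustment that the primary result is biased or its error rate inflated. The documents do not support this: type I error stays near 5%, and the crude standard error already allows for random imbalance. What adjustment adds is a correction for the imbalance that actually occurs in this trial, and a slightly smaller standard error.

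The gain could also be made to look larger than the evidence allows. If baseline data explained 5% or 10% of the variance, power would be 91.4% or 92.8%, but nothing in the article supports those values. A simulation with a latent severity, correlated 0.4 to 0.8 between enrolment and later, gave only 0.3% to 3.6%, or about 90.1% to 91.0% power.

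Two further inferences go too far. One is that the plan itself regards these factors as prognostic. It proposes to look for risk factors and lists subgroups, but asserts no prognostic value. The other is that the plan disregards severity altogether. Two failure criteria are judged against each infant's own starting values. Sicker infants may be likelier to fail, while a high starting rate is likelier to fall, so the net association of heart rate and respiratory rate with failure is uncertain and may be weak.

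Adjusted sensitivity analyses may well sit in a statistical analysis plan that is not shown, and their absence from the article is no criticism. That reply does not reach the primary method, which the article states.

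**Conclusion.** The point holds as a modest efficiency improvement, not as an error. At 582 per group the crude test forgoes about 0.4 to 1.0 power points if severity has an odds ratio of 1.5 to 2.0 per SD (about 1-4% of variance). It forgoes nothing if severity is not prognostic, and about 2.5 points at an odds ratio of 3.0. If all 1400 infants are analysed, crude power is already 94.5% and the gain shrinks to between 0 and 1.7 points. A two-standard-error imbalance, roughly a one-in-twenty event for a single measure, moves the estimate by a small fraction of its confidence-interval half-width. All of these gains rest on an assumed prognostic strength and on the plan's 10% and 5% failure rates. Low priority, but worth doing because the data are collected anyway.

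**What to change.** Before any comparison by arm, pre-specify as the primary estimate a logistic model for treatment failure with arm, enrolment SpO2, heart rate, respiratory rate, respiratory effort, corrected age, prematurity and centre type (tertiary or not). Standardise it to a marginal risk difference with 95% confidence interval and p-value. Standardising keeps the quantity the article promises and avoids replacing it with a conditional odds ratio. Centre type is needed because the SpO2 entry threshold differs between tertiary and other centres, so enrolment SpO2 is partly a marker of where the infant presented. The centre classification should be fixed at the same time, since the Setting section counts five tertiary centres and the Definitions section six. Keep the two-proportion test as the supporting analysis.

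The cost is a sentence or two of wording and no new data. The small downside is that a simple rule is needed for missing enrolment values (for example mean imputation), together with a modelling step the crude test does not require. The article reports 380 of 1400 infants recruited by July 2015 and no interim analysis, so the covariate list could be fixed without knowledge of results by arm.

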### Definitions

All infants aged 0-12 months with symptoms of bronchiolitis (as defined by the American Academy of Pediatrics) - symptoms and signs of respiratory distress and oxygen requirements are eligible [18]. Bronchiolitis is defined as signs and symptoms of respiratory distress associated with symptoms of a viral respiratory tract infection (cough, runny nose, blocked nose, tachypnoea, recessions, nasal flaring, and cyanosis) [3]. Oxygen requirement in room air is defined according to the World Health Organisation recommendation, if transcutaneous haemoglobin oxygen saturation (SpO_2_) is <94 % in room air [19–21]. Six participating tertiary centres in our study have a lower threshold of < 92 % as their standard practice of care. In these sites a threshold of < 92 % was accepted in the randomised design, different saturation thresholds in different centres will be balanced through randomisation across all sites.

***Inclusion criteria*** are infants with a clinical diagnosis of bronchiolitis less than 12 months corrected age (≥ 37 weeks post-conceptional age) with an oxygen requirement in room air of SpO2 < 92 % for tertiary centres and <94 % for regional and metropolitan centres.

***Exclusion criteria*** include those infants with urgent need for respiratory support ( i.e. non-invasive or invasive ventilation or low level of consciousness, apnoea), cyanotic heart disease, basilar skull fracture, upper airway obstruction, craniofacial malformations and infants who are already on home oxygen therapy.

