#### Randomisation process

The enrolment/randomisation process has been successfully tested in the previous pilot study. Randomisation will be achieved by an opaque envelope in sequential order with an allocated infant ratio of 1:1. A computer-based randomisation will be used to allocate infants 1:1 per site. Randomisation can occur at admission or at any time during hospital stay when an oxygen requirement develops.

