#### Other interventions/therapies/nutrition

The use of any medications such as steroids, antibiotics, antipyretics, bronchodilators and hypertonic saline is at the discretion of the attending clinicians and not prescribed in the protocol. These interventions will be recorded in the clinical research form (CRF). Feeding in standard subnasal cannula oxygen therapy is not prescribed and clinicians can choose to administer continuous or bolus feeds or use intravenous fluids. However, in the HFNC therapy intervention arm a nasogastric tube will be inserted, the stomach must be vented at 4 hour intervals, and no oral feeding will be allowed unless in stable weaning phase. Feeding rate should be prescribed as per individual hospital policy using nasogastric (bolus or continuous feeds).

The nursing ratio for both arms will remain according to the standard current ward management already present and as per usual hospital protocol. The nurse/patient ratio is important to maintain, to ensure that infants with the same level of illness do not get increased nursing care due to being on one type of therapy over another. Clinical documentation will be achieved according to individual hospital standards. Admission criteria to intensive care and triggering of medical review (use of early warning tool) will also follow individual hospital rules.

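### Allocation is 1:1 per site and parts of the endpoint are local, but the primary test ignores site: a small, nearly free gain in precision is left unused

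*Protocol article*

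**What the plan says.** **Allocation.** Under Randomisation process: "A computer-based randomisation will be used to allocate infants 1:1 per site". Site is therefore a randomisation stratum. Opaque sequential envelopes are mentioned; blocks are not.

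**Differences between sites.** Case selection and Definitions set the entry threshold at SpO2 below 92 % in tertiary centres and below 94 % elsewhere. Primary outcome definition carries the local target into the third failure criterion and makes the hospital's own early warning tool the fourth. Under Other interventions/therapies/nutrition: "Admission criteria to intensive care and triggering of medical review (use of early warning tool) will also follow individual hospital rules".

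**How the protocol deals with this.** Definitions states that "different saturation thresholds in different centres will be balanced through randomisation across all sites".

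**Primary analysis.** Data analysis says that treatment failure "will be analysed using test of two proportions, and will be reported as the difference, 95 % confidence interval" and a p-value. Site appears there only in the baseline description and in the tertiary and secondary site subgroups. The logistic regression is meant to find risk factors, not to compare treatments.

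**The concern.** When a stratum is used to allocate treatment and also predicts the outcome, the usual advice is to analyse by that stratum. Here the protocol gives reasons to expect failure risk to vary by hospital, because two of the four failure criteria are applied to local standards and entry severity differs by type of centre.

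Balance through randomisation protects the estimate from bias. It does not by itself make the crude standard error the right one. If arms are balanced within each site, differences between sites cancel out of the treatment comparison, but the crude variance still counts them. The interval is then a little wider, and the test a little more conservative, than the design warrants. At stake is a small amount of precision in the primary result, and an open question about site adjustment that is better settled before outcomes are known in an open-label trial.

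**Working it through.** **Inputs from the documents.** Failure risks of 10 % and 5 %, from "a 50 % relative reduction to 5 % with a power of 90 % and type I error of 0.05" (Sample size); 582 per group, 1164 in total; 17 sites (Setting). **Assumed:** a two-sided test, the between-site SD of failure risk, the site sizes, and balance within site except in step 5. The documents give no failure rates by site.

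**1. The plan's own figure.** Pooled two-proportion formula, mean risk 0.075:

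n = [1.960 × √(2 × 0.075 × 0.925) + 1.2816 × √(0.10 × 0.90 + 0.05 × 0.95)]² / 0.05² = (0.7301 + 0.4752)² / 0.0025 = 581.1, rounded up to 582.

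This matches exactly, so the sample size also rests on a crude comparison.

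**2. Excess in the crude standard error.** With site risks p_s of mean p and standard deviation SD, p(1 − p) = mean of p_s(1 − p_s) + SD². With balance within site only the first part is real noise, so the crude SE is too large by the factor f = 1/√(1 − SD²/0.069375), where 0.069375 = 0.075 × 0.925. The size of the crude test is P(|Z| > 1.96 f).

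For power, 0.05/√(2 × 0.069375/582) = 3.238. Crude power is Φ(f × (3.238 − 1.96)) and stratified power is Φ(3.238 f − 1.96).

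| Between-site SD | f | Crude type I error | Crude power | Stratified power |
|---|---|---|---|---|
| 3 points | 1.007 | 4.9 % | 90.1 % | 90.3 % |
| 5 points | 1.019 | 4.6 % | 90.4 % | 91.0 % |
| 8 points | 1.050 | 4.0 % | 91.0 % | 92.5 % |

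**3. Simulation with log-odds heterogeneity.** 17 unequal sites, exact 1:1 within site, about 1164 infants, 20,000 runs per setting. Each cell gives crude, then stratified; interval width is under 10 % versus 5 %.

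| SD of log-odds (control site rates) | Type I error | Power | 95 % interval width, points |
|---|---|---|---|
| 0 (all 10 %) | 5.2 %, 5.1 % | 90.7 %, 90.7 % | 6.01, 6.01 |
| 0.5 (3.6 to 21 %) | 4.7 %, 4.9 % | 90.9 %, 91.2 % | 6.01, 5.97 |
| 1.0 (1 to 36 %) | 4.5 %, 5.2 % | 90.7 %, 91.5 % | 6.01, 5.85 |

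**4. Simulation on the risk scale.** Beta-distributed site risks with SD 8 points (4,000 runs) gave power of 88.1 % crude and 88.8 % stratified. The power difference at the extreme is therefore 0.7 to 1.5 points across the three methods. With no heterogeneity the two tests agree.

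**5. Without forced balance.** Null simulation, 40,000 runs, SD 3, 5 and 8 points. The crude test rejected in 4.9, 4.5 and 3.9 % of trials with exact balance per site, but in 5.0, 4.9 and 4.8 % with simple 1:1 allocation within site. The conservatism thus depends on blocking. Under simple allocation, chance differences in site mix are real noise that the crude standard error counts correctly and stratification can partly remove.

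**6. Size of strata.** 1164/17 = 68.5 infants per site, or about 34 per arm: roughly 3.4 expected failures on control and 1.7 on high flow. Smaller sites will often have no failures.

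**The case against.** The case against making much of this is strong, and most of it stands.

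- **The gain is small.** Under 1 point of power is at stake for an SD of 3 to 5 points. The 8-point case is extreme: its SD exceeds the mean risk of 7.5 %, and the matching beta distribution puts 18 % of sites below 1 % risk and 8 % above 20 %. Nothing in the documents supports that much spread.
- **Strong dependence of failure on site is not shown.** It is a reasonable expectation from local criteria, but no failure rates by site are given. Intensive care access and admission rules are not among the four failure criteria, and escalation from standard oxygen may be to high flow, so their weight in the endpoint is unknown.
- **Blocking is not stated.** Without it the claim of an oversized standard error largely falls away, and only a slight efficiency gain remains.
- **Site type is partly covered** by the tertiary and secondary site subgroups.
- **Sparse strata need care.** A merging rule with no cut-off would add discretion to the primary analysis.
- **The analysis plan, which is not shown, may stratify.** That does not dispose of the point, because the article names the primary test instead of leaving it open.

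A reader might infer that differing thresholds bias the comparison, or that ignoring site inflates false positives. Neither follows. Allocation within site protects against bias from thresholds and local rules, so the protocol's statement about balance is correct as far as bias goes. The crude test is at worst conservative.

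**Conclusion.** The point holds as a minor one about efficiency. The primary analysis does not use the stratum by which infants are allocated, although entry and endpoint rules differ by site. The estimate is unbiased and type I error is not inflated, so the planned analysis is valid.

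Given balance within site, the crude standard error is about 1 to 2 % too large for a between-site SD of 3 to 5 points and about 5 % at an extreme 8 points. The cost is 0.2 to 0.6 points of power in the first range and about 1 point (0.7 to 1.5 by method) at the extreme. These sizes rest on an assumed SD, assumed site sizes and assumed blocking. Without blocking the crude standard error is essentially right, and what remains is a slight gain in precision from stratifying.

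**What to change.** 1. Make the primary analysis a site-stratified Mantel-Haenszel risk difference with 95 % confidence interval and a Cochran-Mantel-Haenszel p-value. This keeps the risk difference as the effect measure. With exact 1:1 allocation in every site the point estimate equals the crude difference, and only its standard error changes.
2. State a numeric minimum size below which a site is merged with others in the same SpO2-threshold class, fixed before outcomes by arm are seen.
3. Before that, reconcile the site counts. Setting lists 5 tertiary centres, while Definitions speaks of six tertiary centres using the threshold below 92 %. List the threshold class of every site, since the merging rule depends on it.
4. State whether allocation within site is blocked.
5. Keep the crude two-proportion test as a supportive analysis, and use the same strata for the secondary proportions.

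The cost is a few sentences in the analysis plan. No new data are needed and the sample size does not change. With 380 of 1400 infants recruited by July 2015 and no interim analysis planned, the change could be fixed in advance of any comparison by arm.

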## Methods

### Study aims

To perform a randomised controlled multicentre trial (RCT) in infants aged less than 12 months (corrected age) with clinically diagnosed bronchiolitis comparing HFNC therapy to standard subnasal oxygen therapy. The primary outcome is treatment failure of HFNC therapy or standard subnasal oxygen.

Secondary outcome measures comprise (a) the rate of transfer of children to higher level care (that is, the rate of transfer from regional hospitals to tertiary centres and rate of transfer from tertiary hospitals to their onsite intensive care unit (ICU) if the primary admission is to their tertiary hospital); (b) length of stay in hospital and (c) health care costs associated with the therapy, transfer and ICU admission (including intubation rates), and overall length of stay; (d) length of oxygen therapy; (e) and measurement of adverse side effects. We hypothesise that HFNC therapy will have a lower failure proportion, reduced transfer rate, reduced length of stay, and lower health care costs associated with the treatment, in comparison to standard subnasal oxygen.

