### Secondary outcome definition

Secondary outcomes are defined as (a) the proportion of infants requiring transfer to higher acuity care, which includes admission to an on-site paediatric intensive care or transfer to a tertiary hospital; (b) length of hospital stay, including intensive care length of stay and (c) intubation rates; (e) associated health care costs for the respective therapy; (f) length of oxygen therapy and; (g) adverse events.

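### Length of stay: the normality switch serves no purpose, and the unstratified rank test it leads to gives no difference with an interval and does not bear on mean stay (minor, secondary outcome)

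*Protocol article*

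**What the plan says.** Under Data analysis, the protocol article expects that "length of stay will likely be non-normally distributed, and as such will be analysed using a Mann-Whitney U test". It then adds the alternative: "if it is normally distributed independent samples t-test will be used". The next sentence sets the reporting style for secondary outcomes: "using confidence intervals of differences as the major method of presentation where possible".

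Length of stay is a secondary outcome, defined as "length of hospital stay, including intensive care length of stay". Study aims states the hypothesis that "HFNC therapy will have a lower failure proportion, reduced transfer rate, reduced length of stay, and lower health care costs". Healthcare cost analysis counts stay in and out of PICU among the resources to be costed, and uses ANCOVA and the bootstrap "to estimate a confidence interval around the mean difference". Randomisation process states that allocation is 1:1 within each site.

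**The concern.** A rank test and a t-test answer different questions. Mann-Whitney asks whether an infant on HFNC tends to stay longer than a control infant. The t-test compares mean stay. A rule that picks between them after seeing the data leaves the quantity of interest open until then.

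Three further points concern the branch that will in practice be taken:
- The Mann-Whitney test as named gives a p-value, not a difference with an interval, although intervals are to be the main form of presentation.
- Costs are compared on means, and stay is one of the costed resources. The stay result and the cost result would therefore rest on different quantities, with nothing in the article to link them.
- The named test takes no account of site, although allocation is balanced within site. Stay may well differ between sites: tertiary centres work to a 92 % saturation threshold and the others to 94 %, for both entry and weaning.

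At stake is how a secondary outcome and its link to cost are read.

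**Working it through.** **1. The plan's own figure.** The inputs, from Sample size, are "a 50 % relative reduction to 5 % with a power of 90 % and type I error of 0.05", from a 10 % baseline. With pooled variance, a two-sided test and no continuity correction:

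n = [1.960·√(2·0.075·0.925) + 1.282·√(0.10·0.90 + 0.05·0.95)]² / 0.05² = (0.730 + 0.475)² / 0.0025 = 581.1, rounded up to 582.

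This matches "582 participants per group are required, resulting in a total sample size of 1164 patients". No power is stated for length of stay, and nothing below changes this figure.

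**2. Does the switch matter?** The documents give no distribution for stay, so one is assumed here: log-normal, median 48 h, log-SD 0.6, plus 96 h extra after failure, 582 per arm. The rule was run as Shapiro-Wilk in each arm, then t-test or Mann-Whitney.

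| Data, no treatment effect | Two-step rule | Always Mann-Whitney | Always t-test |
|---|---|---|---|
| Skewed | 4.8 % | 4.8 % | 4.75 % |
| Normal | 5.3 % | 5.3 % | 5.1 % |

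Normality was rejected in 100 % of the skewed trials, so the t-test was never reached. With normal data, mean and rank effects have the same sign in theory. Sample signs differed in only 2-7 % of trials, which is noise near zero.

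**3. Can rank and mean diverge?** Suppose HFNC halves failure from 10 % to 5 %, each failure adds E hours, and HFNC lengthens every stay by s hours. Then

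difference in mean stay = s − 0.05·E.

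With E = 96 h, median 48 h and log-SD 0.6:

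| s (h) | Mean difference (h) | P(HFNC stay longer) | Directions |
|---|---|---|---|
| 0 | −4.8 | 0.479 | agree |
| 3 | −1.8 | 0.507 | opposite |
| 4 | −0.8 | 0.517 | opposite |
| 6 | +1.2 | 0.535 | agree |

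The mean changes sign at s = 0.05·E, which is 2.4 h for E = 48 h and 6 h for E = 120 h. Over a grid of medians 36-48 h, log-SD 0.6-0.9 and E 48-120 h, reversal appeared only for shifts of about 2-6 h, with P(HFNC longer) between about 0.50 and 0.55.

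**4. How often in single trials?** A second assumed model used ward stay of median 44 h (log-SD 0.55), ICU stay of median 120 h (log-SD 0.5) and 700 per arm. The table gives the share of trials in which the two results have opposite signs.

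| ICU use, control vs HFNC | s = 0 | 2 h | 4 h |
|---|---|---|---|
| 10 % vs 5 % | 7 % | 39 % | 52 % |
| 12 % vs 6 % | 4 % | 29 % | 59-60 % |

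With no treatment effect at all the share is already 20 %. In the 12 % vs 6 %, 4 h case, a significant rank result favouring control came with a mean favouring HFNC in about 5 % of trials. Both tests were significant in opposite directions in at most 0.2 % of trials in any setting.

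**5. Should the mean replace the rank test?** Power in the second model:
- ICU use falls from 10 % to 5 % and ward stay is unchanged: rank 28 %, mean 48 %.
- Ward stay shortens by 10 % and ICU use is 10 % in both arms: rank 83 %, mean 51 %.

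Neither summary dominates.

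**6. What does site add?** With an assumed between-site log-SD of 0.35, power was 85 % for the site-stratified rank test and 75 % for the unstratified one. When sites did not differ, stratifying lost nothing.

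**The case against.** The strongest reply is that the analysis is already settled. Mann-Whitney is the declared default, the t-test is a fallback that skewed stay will not reach, and error rates hold. That is right, and it removes most of the weight from the switch itself.

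A reader might infer that the data-driven choice could flip the conclusion, or that the stay result will contradict the cost result. The documents do not support either reading:
- Opposite directions need skewed data, where the rule gives only Mann-Whitney. Where it gives the t-test, the two comparisons agree in direction.
- Reversal needs an HFNC-only lengthening of ordinary stays. The documents give no such figure, and with none the share of opposite signs is 4-7 %.
- The weaning rule is no basis for a lengthening, because Weaning sets a four-hour room-air period in both arms. The HFNC limit on oral feeding before stable weaning is a more plausible route, but no duration attaches to it.
- Cost also includes transfers, device resources and DRG weights, so it is not a rescaling of mean stay. A mean difference that is not significant contradicts nothing.

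It can also be said that a Hodges-Lehmann interval is the usual companion to Mann-Whitney, and that naming it may be left to the analysis plan. That is fair, and it would meet the interval commitment. It would still estimate a shift rather than the mean stay that enters the costs, and it would not bring in site.

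**Conclusion.** The point holds as a minor one. The conditional clause makes the comparison depend on the observed distribution for no gain. The test that will be used, an unstratified Mann-Whitney test, leaves three things undone: a difference with an interval, a statement about mean stay to set beside the costs, and use of the allocation within site.

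The switch costs essentially nothing in error rate. Stratifying by site was worth about 10 percentage points of power (85 % against 75 %) under the assumed between-site spread, and nothing if sites are alike. Divergence between rank and mean is possible under the planned 10 % to 5 % reduction, but only within a band of assumed shifts, and the effects are small. Every figure on stay rests on assumed distributions. The outcome is secondary, and the primary analysis, the sample size and alpha are unaffected.

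**What to change.** In Data analysis:
- Delete "if it is normally distributed independent samples t-test will be used".
- Keep the Mann-Whitney test for length of stay whatever the distribution looks like, stratified by site.
- Always report beside it the difference in mean stay with a bootstrap 95 % confidence interval, resampling within site and arm.
- State that the rank test supplies the p-value and the mean difference is the estimate that links to cost, so that neither can be chosen afterwards.

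The cost is one or two sentences and a few lines of code; the bootstrap is already planned for costs. The downsides are that the mean is sensitive to a few very long stays, which the rank test beside it helps to show, and that two summaries must be reported and may not agree.
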